### Study type

We will conduct a randomized controlled trial , comparing [1] standard-of- care (n = 108) with [2] standard-of-care plus a mobile phone-based SMS intervention (n = 108) for 6 months among patients with newly diagnosed type 2 diabetes receiving treatment at the OPD of BIHS hospital in Dhaka City (Figure 1).

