### Sample size

Assuming that standard care with metformin reduces HbA1c by 1% on average and the intervention adds another 0,5% [15,16]. Assuming a SD of 1, which seems reasonable and an alpha error level of 5%, the two-tailed calculation gives a power of over 90% with only 90 participants in each arm of the study. Considering 20% loss of follow up by 6 months total sample size required for this study will be 216.

**Inclusion criteria:**Diagnosed as type 2 diabetic patient according to WHO criteriaCurrently on oral Metformin monotherapy and able to afford cost for 6 months treatmentPatients with a personal mobile phonePatients who know how to retrieve/read SMS on mobile phone (Bangla with English alphabets)Willingness to receive SMS for 6 months at least one SMS per day.Patient registered with the BIHS health centre and lives in Dhaka City.Provide written informed consent and agree for a follow up visit after 6 months. (SMS reminders will be sent for the follow up visit).

**Exclusion criteria:**Patients with other types of diabetes, such as diagnosed as type 1 diabetes, gestational diabetes.Patients whose clinical condition might have interfered with the study such as mental illness, other serious illness or co-morbidities requiring hospitalization.Patients unable to give their informed consent or agree for follow up visit.Patients who do not own a mobile phone or cannot read SMS messages.Patients who reside outside Dhaka city.

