### Data collection and intervention

Data will be collected at baseline (0 month) and after 6 months through questionnaires, physical measurements and blood tests (Figure 1). We will send out mobile phone SMS to patients in the intervention group for medication reminders and health education about diabetes, its complications, diet and physical activity. SMS content has been developed using different national and international guidelines for diabetes and will be field tested for clarity and contents. The patients will be encouraged to send messages/call the study team for any queries encountered in response to the text messages. The study team will then call patients who had a problem within 2 working days. Study staff will maintain a study register to record all SMS responses and other mobile phone communications with patients in a study log.

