### SMS development and testing

The SMS messages were developed by a team comprising of general physicians, an endocrinologist, an epidemiologist, a nurse and a undergraduate student. After developing the SMS messages in Bengali, we sent these messages to several individuals in the pre-test stage including persons who can only read SMS and have no formal education qualifications. After receiving the feedback, we tried to make the contents of the SMS suitable for the general population. We will ensure that all our participants in the study can read the SMS messages by themselves or someone in the family who can describe the messages to them if they do not understand. At the end of the follow-up we will evaluate if they failed to understand any of the SMS.

*Most of the 90 SMS were developed based on the principles of behavioural learning theory and transtheoretical model of behavioural change* [17-19]. *All participants in the SMS intervention group will receive the 90 SMS randomly, once a day over the 6 months period. Some examples of the SMS are provided below:*Diabetes is a serious disease, but it can be easily controlledCheck your blood pressure at least for 2 times in a year and write it downRegular physical exercise or walking habit will help to bring your blood glucose to normal levelDon't forget to take your medication as advised by your physicianA planned diet and weight control will help to reduce the risk of heart disease and strokeDo you have any appointment with your doctor in this month? Then do not miss it.Have you done your physical activity, walking for 30 minutes or exercise today? If not then do it when you become freeIf you are stressed, stop your work. Go for a walk and relax!A healthy diet will keep you healthy and happyDid you take all your medication today as advised by your physician?Visiting your doctor timely is essential for youDiscuss with your doctor about your concerns and worries about your conditionAwareness about your disease and following your doctor's advice can make your life healthy and happyTaking medication timely will help to keep your blood sugar in control and avoid complicationsDiabetic people with disciplined life enjoys a healthy longer life.

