Secondary outcomes will be compared with the χ2 test for categorical outcome. Fisher's exact test for outcomes will be used to estimate p values. Logistic regression will be used for Quality of Life (QoL) and other continuous variables. In the subgroup analysis in the intention-to-treat population, we will compare the intervention groups within each subgroup of patients with the χ2 test for the categorical outcome and logistic regression for QoL. For all models, the results are expressed as an estimate of effect size, with 95% CIs and p values. The response type throughout the study period will be analysed by categorising time since random allocation to the 6 months and doing a χ2 test between time and response type. All statistical analyses will be done using SPSS version 20 (IBM Corporation, USA).

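### The chi-square test of time by response type assumes independent entries, but the plan allows the same participant to be counted several times, so its p value may be too small or too large

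*Protocol article*

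**What the plan says.** The closing paragraph of Data analysis in the protocol article names a specific method, an ordinary chi-square test on a two-way table. The time axis is set as follows: "The response type throughout the study period will be analysed by categorising time since random allocation to the 6 months". The article gives no definition of response type, does not say what one row of the table represents, and names no method for repeated observations.

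The only data described as accumulating through the study are in Data collection and intervention. There, "The patients will be encouraged to send messages/call the study team for any queries encountered in response to the text messages", and "Study staff will maintain a study register to record all SMS responses and other mobile phone communications with patients in a study log". Questionnaires, physical measurements and blood tests are taken only at baseline and 6 months. Under SMS development and testing, participants in the intervention arm "will receive the 90 SMS randomly, once a day over the 6 months period", so occasions to respond recur. Study type gives "standard-of-care plus a mobile phone-based SMS intervention (n = 108) for 6 months".

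**The concern.** A Pearson chi-square test compares the table with what independent entries would produce. Nothing in the article restricts the table to one entry per participant. If a participant tends to send the same kind of reply each time, the entries are correlated, and the reference distribution no longer applies.

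The direction of the error depends on timing. If everyone replies equally often in every month, personal differences cancel between months and the test is too cautious. If participants concentrate their replies in different months, differences between people appear as differences between months, and the test rejects too often. A reported change in response type over time could then reflect a few frequent repliers, or a real change could be missed.

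**Working it through.** **Inputs from the article.** 108 participants in the SMS arm (Study type); 20% loss and a 5% level (Sample size). 108 × (1 − 0.20) = 86.4, so 86 to 108 participants. The article gives no figure for this analysis, so there is none to reproduce. Its power statement (over 90% with 90 per arm) reproduces at 91.8% and has no bearing here.

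**Inputs assumed.** T = 6 monthly categories; two response types with shares 70% and 30%; m = 12 replies per participant (also 3); within-person correlation ρ = 0.1, 0.3, 0.5; no true time effect.

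**Approximation.** Let s be the chance that two replies from the same participant fall in the same month. The expected chi-square statistic is multiplied by about

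F = 1 + ρ (m − 1)(T·s − 1)/(T − 1).

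With 5 degrees of freedom the 5% critical value is 11.07, so the false-positive rate is about P(χ²₅ > 11.07/F).

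- Even replies, two per month: s = 1/11, so F = 1 − ρ.
- Random months: s = 1/6, so F = 1.
- Mildly uneven (month preferences drawn from Dirichlet(2)): s = 3/13, so F = 1 + 0.846ρ.
- Strongly uneven (Dirichlet(0.5)): s = 1.5/4 = 0.375, so F = 1 + 2.75ρ.
- Strongly uneven, 3 replies: F = 1 + 0.5ρ.

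| Reply pattern | Formula, ρ = 0.1 / 0.3 / 0.5 | Simulation |
|---|---|---|
| Even, 12 replies | 3.1% / 0.7% / 0.05% | about 3% / 0.5–1% / 0.1–0.2% |
| Random months, 12 | 5% / 5% / 5% | about 4–6% throughout |
| Mildly uneven, 12 | 7.0% / 11.6% / 16.9% | about 7–8% / 12–13% / 17–18% |
| Strongly uneven, 12 | 12.2% / 30.0% / 45.9% | about 12–13% / 29–31% / 44–46% |
| Strongly uneven, 3 | 6.1% / 8.7% / 11.5% | about 5–12% overall |

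Using 86 or 108 participants makes little difference, because the number of participants does not enter F.

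**Other settings.** With three response types, 6 replies and 108 participants, simulation gave 3.1%, 0.4% and 0.0% (one reply every month), 8.8%, 17.9% and 34.5% (strongly uneven), and 26.8%, 69.9% and 88.8% (all of a participant's replies in one month). The last pattern is an extreme. With zero correlation the rates were about 4% to 6%, so clustering is what drives the error.

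**The other reading.** If response type means answers at baseline and 6 months, each person appears in both columns. Then T = 2, m = 2, s = 0 and F = 1 − ρ. With 1 degree of freedom (critical value 3.84) the rate is 3.9%, 1.9% and 0.6%; simulation with 86 people gave 3.3%, 2.5% and 0.7%. The test is again not at its nominal level, this time only in the conservative direction.

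**The case against.** The strongest reply is that the counting unit is inferred. The article never says that the register feeds this test, and a condensed article may leave the definition to the full protocol. That stands as a limit on the finding: the link to the log is the natural reading, not a stated fact. It does not rescue the test, because the baseline and 6-month reading is paired and no text restricts the table to one entry per person.

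The article also gives no support for many replies per participant. Contact is invited for queries, and most of the example messages ask for no reply. With one or two replies each, simulated rates were about 4% to 7%, even with strongly uneven timing. With random reply months the test is close to nominal. A reader might infer that the p value is certainly wrong, or that a rate near 46% is to be expected; the documents support neither. The responding population is also unclear, since Ethics gives all participants access to SMS and calls.

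A further objection concerns the remedy and also stands. A change in who replies is a change in composition, which clustered standard errors do not remove. In a simulation with no within-person change but selective cessation of replies (ρ = 0.3, 86 participants, 200 runs), a GEE with robust standard errors still rejected in 60% of runs with an independence working correlation and in 14% with an exchangeable one.

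Finally, response type over time is not among the article's objectives, hypotheses or outcomes, and the article does not call it a measure of engagement.

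**Conclusion.** The point holds in conditional form. The plan names a test that needs independent entries, and on either natural reading of response type it does not have them. The p value may be too small or too large. Under the assumptions above, the false-positive rate at nominal 5% runs from under 1% with even replies, through about 5% with random months, to 12% to 46% with strongly uneven timing and 12 replies each. It is about 5% to 12% with 3 replies each. Reply counts, timing and within-person correlation are all assumed.

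The consequence is small. This is one process analysis; a reader might infer that it weakens the trial's main result, but it has no bearing on the HbA1c comparison. It is worth correcting because the correction is cheap.

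**What to change.** First, define response type and the counting unit, and say whose responses are counted. Then do one of the following:

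- Replace the chi-square with a logistic or multinomial model of response type on month, fitted by GEE clustered on participant with robust standard errors.
- Report monthly proportions with bootstrap confidence intervals that resample participants, and give no p value.

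Both describe the mix of replies in each month; they correct the standard errors but not a change in who replies. So also report the number of participants replying each month. If a within-person trend is to be claimed, use a within-participant model (conditional or mixed).

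The cost is a few lines of analysis text and slightly more analysis work. Ethics already assigns each participant a unique subject ID, so no new data should be needed, provided log entries carry it.

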### Health economic analysis

Primary analyses: We will measure the economic impact of the mobile phone based SMS interventions. All relevant costs incurred during the observation period will be assessed and compared between the two study arms. Cost for the intervention excluding the costs caused by the study will be considered. To calculate the economic cost of intervention we will use the CostIt (Costing Interventions templates) tool developed by WHO. The CostIt tool provides a set of separate templates for the reporting and analysis of costs at the programme, hospital, primary health facility and household levels. The following steps will be used:Define the costs (identify all direct and indirect costs)Evaluate the total cost of SMS intervention

The data collection tools have been designed to capture cost measurement for medication, transportation, consultation, blood tests, days lost due to illness, hospitalization costs and other associated direct and indirect costs. Costs associated with mobile phone SMS interventions will be recorded in a separate register and used for data analysis in measuring the costs which includes costs for personnel, materials and supplies, operating costs, maintenance costs, utilities, capital costs and other indirect costs. Cost for standard of care, costs for the SMS intervention and accessing the SMS intervention will be calculated. Also, costs associated with productivity gained due to improvement of health conditions will be assumed.

In order to estimate the impact of mobile phone SMS on diabetes control, we will conduct a within-trial cost-effectiveness analysis which examines cost associated with health gains. The measure of effect will be units of HbA1C reduction. In addition, a cost effectiveness-analysis will be conducted where health gains are expressed in terms of health-related quality of life as measured by the EQ-5D questionnaire. The within-trial cost effectiveness analysis will be performed with support [name] and his team at the Institute of Health Economics and Health Care Management of the Helmholtz Zentrum Muenchen, Germany.

### Ethics

All participants will be explained about the objectives, importance, risks and benefits of the research before recruitment. Participation will be completely voluntary and an appropriate written informed consent will be obtained from all participants. All participants will be given a copy of the consent form and contact details of the study coordinator for their future questions and concerns. All participants will have access to send SMS or call the study team for advice and suggestions during the study period as a compensation for participating in the study.

All participants will be assigned a unique alpha-numeric subject ID. All data-set, biological samples and clinical investigations performed for the study will be identified by the unique subject ID given to each participant. Staff at the laboratory will not have access to the confidential codes linking the subject IDs to the personal identifier. The hard-copies of all the data collection forms will be stored and locked at icddr, b and access to these files will only be given to the PI’s, and authorized staff. All computer databases will be protected by firewalls and a password-entry system. Only PI and designated staff will have access to database and files matching personal identifiers to subject IDs for the purposes of contacting study participants for follow-up. Publications and scientific presentations of the findings from the study will be presented in aggregates and identity of individual participants will be kept confidential.

Local health authority in the study site will be informed of the study and discussions will be held about management of any clinical problems arising during the study. Any participant who is discovered to have a chronic disease or risk factor(s) that require management will be appropriately informed about the condition and its implications by a medical member of the study team. They will then be referred to an appropriate service for further management.

This study has been approved by icddr, b Research Review Committee (PR# 13018) on 15 April, 2013 and Ethical Review Committee on 28^th^ May 2013.

## Discussion

This article describes the protocol for a randomized control study to measure the effects of mobile phone SMS on diabetes knowledge, medication adherence, clinic attendance and glycemic control for patients with type 2 diabetes in an urban area of Bangladesh. This study is the first in developing countries, to the best of our knowledge, to measure the impacts of mobile phone SMS for diabetes. One of the most significant barriers to effective treatment of type 2 diabetes is a lack of awareness and education about diabetes, its complications and optimal way to treatment which can be addressed by mobile phone interventions for knowledge generation, awareness and behaviour change communications.

Although a nationally representative and multi-center, cluster randomized controlled trial is optimum from the methodological perspective for this study, due to lack of resources and time constraints we have to limit our study to a single centre. However, data gathered from this study will allow us to evaluate the effectiveness and cost-effectiveness of SMS interventions in reducing HbA1c from within the trial. In recent years there are numerous attempts to integrate mobile phones for health interventions and this study can direct future research in Bangladesh for diabetes management in clinical settings using innovative mobile technologies.

Participants will be identified before randomization in an attempt to avoid bias. We will initially inform the participants about the study and after obtaining informed consent will conduct the interviews and obtain blood samples for HbA1c. We will then randomize the participants using a random allocation software to the intervention and control arms.

Using SMS as tools for medication and appointment reminders; disseminate health information and life-style messages are easy technology that can be applied by persons with minimum technical knowledge and skills. In this study, we will send the SMS to participants using a internet modem with build-in software for sending SMS and bulk messages. As the SMS will be written in Bengali using English alphabets we assume it will not be very difficult for participants to read and understand. However, as the literacy rate of Bangladesh has been reported to be only 62.5%, the ability to read the SMS messages were considered in the inclusion criteria which does not automatically translate into the ability to understand the contents of the SMS.

Outcomes between the two groups will be measured after 6 months by standardised questionnaires, review of medical records and patient medication book, physical measurements and biological sample to determine effects of the intervention on outcomes. Although the short time period will not allow us to evaluate the impact of mobile phone SMS on development of diabetic complications, this will provide us with a baseline data which can be tested on future extension of this study. Furthermore, we expect that the SMS will have some impact on lifestyle outcome measures than on metabolic parameters because a lifestyle change must occur before we can measure an effect on metabolic parameters. We expect the metabolic parameters to have stronger long-term effects. Also, it is expected that the SMS intervention will possibly help to increase knowledge about diabetes and its complications, leading to better medication adherence which ultimately might lead to better glycaemic control.

Although we originally intended to perform detailed health economic analysis for this study we considered that secondary analyses will be performed depending on positive results of the primary analyses and the availability of human resources. In the secondary analyses, we will attempt to combine the short-term evidence from the SMS intervention study with expected long-term effects and outcomes for the patients. These analyses will use decision-analytic models such as Markov or state transition models to describe the disease process.

Each unit of HbA1c reduction will be converted to a health outcome unit for example DALY (Disability Adjusted Life Years) gained and compared between non-intervention and intervention in terms of financial unit. The DALY extends the concept of potential years of life lost due to premature death (PYLL) to include equivalent years of “healthy” life lost by virtue of being in states other than good health. DALYs lost due to diabetes will be calculated as the sum of the years of life lost due to premature mortality (YLL) in the population and the equivalent “healthy” years lost due to non-fatal health conditions (YLD) : DALY = YLL + YLD.

When measuring the burden of diabetes, or the decrement in health due to diabetes, each year of life lost is given a weight of 1. Years lived, but in states less than full health, are given a weight between 0 and 1, with 0 representing full health. Using standardized population models such as WHO developed PopMod [20], we will calculate the benefits of the SMS intervention compared to standard of care. The outcome will be measured in terms of costs and effects. For both the standard of care and SMS intervention we will measure the expected costs and expected outcomes and the results expressed as ratio of difference in expected costs and effects.

SMS for health promotion have been well-accepted by beneficiaries and may be an effective tool for providing diabetes health education, clinic and appointment reminders, medication reminders and building awareness about the disease [12-14]. A recent study in Netherlands showed that SMS reminders improved adherence of type 2 diabetes patients, especially the precision with which the patients followed their prescribed regimen and that it was well accepted by the patients [21]. Numerous issues must be considered when designing and implementing client-centered programs, including mobile phone access, sharing of phones, language and literacy, privacy, and technological challenges. More information is needed about best practices for developing content for text message delivery and the optimal timing of messages [22].

